#### Mobility

The Keele Assessment of Participation [66] will be administered at baseline and 12 months to assess any change in mobility and community participation in intervention and control groups. This is the primary outcome measure for community participation. Secondary measures of mobility include frequency of socialization, frequency of trips out of the home, both driven and others reported at the 12-month visit. Uptake of alternative forms of transport will also be compared.

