### Study procedures

Drivers interested in participating will be asked to contact the study centre by phone and complete a short interview to confirm eligibility. Participants are limited to residents of the Hills and Hornsby-Kuringai Shires so local transport services can be integrated into our intervention program. The program is only available in English and requires involvement of the participant in the education and planning so participants who do not have conversational English and those with evidence of a significant cognitive deficit will be excluded from the study [31]. As driving will be measured objectively, we require that participants are the primary driver of their own car and that they agree to have the in-vehicle monitoring device installed for a period of 12 months. The eligibility criteria are therefore; aged 75 years or older and resident in the Hills Shire, holder of a current drivers’ license, primary driver of their own vehicle, speak conversational English and two or less errors on the Short Portable Mental Status Questionnaire [31].

A baseline assessment will characterise the drivers enrolled in this study and will be conducted during a home visit lasting 1.5-2 h. Comorbidities [32], medication and alcohol use, presence of depressive symptoms (Geriatric Depression Scale [33]) and mood (Positive and Negative Affect Scale [34]) will be assessed by questionnaire. Driving relies heavily on cues from vision and we will assess vision using a measure of contrast sensitivity (Mars Perspectix letter chart) [35]. Contrast sensitivity appears to be a better predictor of driving performance than high contrast visual acuity. Owsley et al. [36] showed that contrast sensitivity was associated with crash involvement whereas visual acuity and glare sensitivity showed no significant associations. There are a number of measures of cognition relevant to driving abilities [37] and the Trail Making Test Part B is selected as it is portable, easy to administer, normative data are available [38] and it is predictive of driving performance [39]. The Trail Making Test Part B is a test of visual scanning and processing and executive function [40]. Longer times to complete the TMT Part B have been associated with poor driving performance in a number of studies [41-44].

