### Intervention

We propose to work with a group of older drivers to help them make informed choices about transport, thereby promoting safety but maintaining mobility and community engagement. Educational programs have been shown to increase use of safe driving strategies [51] and have included classroom modules [52], one-on-one counselling [53], video programs [54] and home based CD-rom or workbooks [6]. The KEYS program was selected as the basis for our intervention as it is well grounded in social-cognitive theories of behaviour [53]. While not proven to be protective against crash risk in a small trial in the US [55], Owsley demonstrated that the KEYS educational program, administered to a group of older drivers with visual acuity deficits or slowed visual speed of processing, increased self-reported safe driving practices [56].

The KEYS program has been adapted for the Australian setting and comprises two one-on-one sessions conducted in the participant’s home. The education is not ‘one size fits all’, instead it will be customised to meet the stage of behaviour change of the participant using the Precaution Adoption Process Model [57]. Understanding the stage of precaution adoption and self-regulation behaviour of each individual will allow the educator to tailor the approach and educational content. This targeted education aims to move participants through the stages of behaviour change towards adoption of safer driving practices [58].

The skill-building component raises the drivers’ awareness of their own skills and abilities and helps drivers match their driving skills to their driving exposure. The educator assists drivers translate this information into appropriate self-regulatory strategies that aim to promote safe driving for as long as possible. Finally, the intervention will build participant’s confidence in their ability to make changes to their driving habits. Strategies will include giving examples of other older drivers who have changed the way they drive and working with participants to set goals regarding changing their driving.

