### Outcome assessment

#### Safety

A primary aim of this research will be to determine if driving safety is promoted through reduced driving exposure and fewer rapid deceleration events in the group participating in the program. An in-vehicle monitoring device or ‘black box’ will be installed into participants’ own vehicles by a mobile technician. The device consists of an in-vehicle data logger, three-axis accelerometer and GPS receiver, hard-wired to the vehicle which transmits time-stamped data on changes in speed and location every 20 s during vehicle operation. Data will be transferred weekly to a secure server and the devices will remain in the participants’ vehicle for 12 months.

The in-vehicle monitoring system has been validated in pilot study and laboratory experiments [60]. The device also has recently been field tested in 30 vehicles in metropolitan Sydney. Data quality was accurate and validation studies found 97% of trips were captured [61]. Importantly the device requires no involvement from the participant and in previous studies was well received by those involved. Rapid deceleration events will be defined as 500 m-G or higher deceleration [Meredith 2012]. Deceleration has been proposed as an indicator of a possible near–crash event [62]. and is a useful outcome measure when alternative outcomes such as crashes are infrequent and require large sample sizes. In-vehicle monitoring is an objective measure and all data will be processed by research assistants not involved in delivery of the intervention who will be blinded to treatment allocation. As the program is individualised, we hypothesise that the effect of the program will be greater in those participants with worse levels of function and this is a pre-specified sub-group analysis based on scores on the DriveSafe/DriveAware assessment {Kay, 2009 #2230} [48].

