Secondary outcome measures of driving exposure include night driving and radius of travel from home. These variables will also be constructed from data collected by the in-vehicle monitoring system. Self-reported driving habits will be used as secondary outcome measures and survey responses compared at the 12-month time-point, adjusting for baseline. We will use an adapted version of the Driving Habits Questionnaire (DHQ) [63] and instruments developed for Australian populations by Baldock et al. [9] and Sullivan et al. [64] to assess self-reported driving habits, confidence in driving and self-reported avoidance of particular driving conditions. Other secondary outcomes include presence of depressive symptoms [65] and mood [34].

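### The driven part of the trip-frequency mobility outcome rests on unblinded participant report, although the in-vehicle device already logs those trips for 12 months

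*Protocol article*

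**What the plan says.** Under Mobility, the Protocol article makes the Keele Assessment of Participation the primary measure of community participation, collected at baseline and 12 months. It then adds secondary measures: "Secondary measures of mobility include frequency of socialization", followed by "frequency of trips out of the home, both driven and others reported at the 12-month visit". No device source and no baseline value is named for trip frequency.

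Under Study procedures, participants must agree to have the "in-vehicle monitoring device installed for a period of 12 months". Under Safety, the device "transmits time-stamped data on changes in speed and location every 20 s during vehicle operation", and "validation studies found 97% of trips were captured". Device data are processed by staff who do not deliver the programme and are blinded to allocation.

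The same section builds two secondary measures of driving exposure, night driving and radius from home, from the device data. It treats the questionnaires separately: "Self-reported driving habits will be used as secondary outcome measures", compared at 12 months with adjustment for baseline.

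**The concern.** The intervention is two one-to-one home sessions in which the educator and the participant set goals for changing driving. The trial's stated aim is less driving exposure with mobility maintained. Intervention participants therefore know their allocation, and when asked at month 12 how often they drive they may answer in line with goals they agreed to. Control participants have no such goals. A difference between arms in reported driven trips could then be partly or wholly a difference in reporting.

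The item lists driven and other trips together, so it bears on whether other transport replaced driving. If the driven part is biased, that replacement can look larger or smaller than it was. For this part an objective source already exists within the trial.

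**Working it through.** The point concerns the source of a measure. The plan states no figure for it, so there is none to reproduce. The first step compares sources; the second is for scale only.

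**1. Source of each driving-related measure (Protocol article)**

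| Measure | Role | Source | Open to participant reporting bias? |
|---|---|---|---|
| Kilometres, rapid deceleration events | Primary | Device, 12 months, blinded processing | No |
| Night driving, radius from home | Secondary, driving exposure | Device | No |
| Driving habits, confidence, avoidance | Secondary | Questionnaire, baseline-adjusted, labelled self-report | Yes, openly so |
| Trips out of the home: driven | Secondary, mobility | Report at 12 months | Yes, with a device alternative |
| Trips out of the home: other | Secondary, mobility | Report at 12 months | Yes, with no device alternative |

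Only the fourth row has both a reporting problem and an objective count of nearly the same quantity already in hand. The wording could be read so that the report applies only to the other trips. The source for driven trips would then be unstated, and the same clause would need the same edit.

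**2. What a differential reporting bias could do (assumed values)**

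Inputs: 178 per arm and a two-sided 5% level, from Sample size and statistical analysis. The bias b, in SD units, is an assumption. The true difference is set to zero and a normal approximation for two means is used.

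- Standard error in SD units: √(2/178) = 0.106.
- Smallest difference detectable with 80% power: (1.960 + 0.842) × 0.106 = 0.30 SD.
- False-positive rate: P(Z > 1.96 − b/0.106) + P(Z < −1.96 − b/0.106).

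| Assumed bias b (SD) | b/0.106 | False-positive rate |
|---|---|---|
| 0 | 0 | 5% |
| 0.05 | 0.47 | 8% |
| 0.10 | 0.94 | 16% |
| 0.20 | 1.89 | 47% |
| 0.30 | 2.83 | 81% |

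A reporting bias well below the detectable difference would already distort the test. Whether a bias of any such size exists cannot be learned from the documents.

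**The case against.** The strongest reply is that little depends on this item. The reading of less driving with mobility kept rests on two primary outcomes, device-measured exposure and the Keele score, so a spurious fall in reported driven trips could be seen against objective kilometres. That stands, and it keeps the point minor.

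The second reply is that the device does not count the same trips. It is wired to the car, and eligibility requires only the "primary driver of their own vehicle". Trips the participant drives in another car are missed, and trips by another driver of the car are counted. A participant who hands over the wheel but rides in their own car still generates a logged trip, and this could differ by arm. This also stands. The device count is not an exact substitute, but the trial already accepts the same limit for its primary exposure outcome.

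Third, taking driven trips from the device and other trips from report mixes units and time windows. That is a reason to keep self-reported driven trips as well, so that driven and other trips can still be compared within one source.

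A reader might infer three stronger things that the documents do not support:

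- **That the bias reaches the driving-exposure outcomes.** Those come from the device.
- **That the parent programme shows self-report moving without real change.** The Intervention section says it "increased self-reported safe driving practices" and was not proven protective against crashes in a small trial. Crashes are rare and are not the objective counterpart of those practices, so this is a reason for caution and not evidence of misreporting.
- **That a gap between self-report and device that differs by arm would prove reporting bias.** Car sharing and mismatched time windows could also produce it.

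**Conclusion.** The point holds as a low-cost improvement to the driven component of one mobility secondary outcome. That component is reported by participants who know their arm and have set goals about their driving, while a year-long vehicle log with blinded processing is available and not named as its source. Differential reporting could bias the component. Its direction and size are undocumented, and the rates shown above rest on assumed values.

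The conclusion assumes that intervention participants know their allocation, which follows from the nature of the programme, and that trip capture here resembles the 97% found in earlier validation, which was not measured in this trial. It does not extend to kilometres, rapid deceleration events, night driving or radius. The driving-habit questionnaires are plainly labelled self-report and need only be interpreted as such.

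**What to change.** In the Mobility section, make these changes:

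- **Driven trips:** define frequency as the number of device-recorded trips over 12 months. Analyse it with the Poisson or negative binomial model already named for count data, accounting for weeks of monitoring, for example through an offset.
- **Other trips:** keep participant report at 12 months.
- **Self-reported driven trips:** keep as a supportive measure, so that driven and other trips can be compared within one source.
- **Interpretation:** present self-reported driven trips and driving habits as self-report.
- **Limitation:** state that the device counts the car's trips, including those by other drivers, and misses trips in other cars.

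The cost is a few lines of wording and one derived variable from data already collected. The downside is the vehicle-level limit, which the primary exposure outcome shares.

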### Sample size and statistical analysis

Previous research has found that approximately 12% of older drivers report crash involvement during a 12-month period [67]. However, near misses are approximately 18 times higher than crash rates [68]. We may therefore expect to document approximately 370 incidents (crashes and near misses) during our period of observation (rate 0.73 per person/year)[68]. With a 5% level of significance and 80% power, we require 178 in each arm to detect a 20% reduction in combined crash and near miss rates (i.e., IRR=0.80). Allowing for drop-outs rate of 5%, we will enroll 380 into the program (190 in each arm). We will be able to measure a difference of 6 km in daily distance travelled (~30% reduction), using daily mileage in a population of older drivers [28]. Differences in the Keele Assessment of Participation will also be well served by this sample size.

An intention-to-treat approach will be used for all analyses. Driving exposure (kilometres travelled) and the number of rapid deceleration events (RDE) during 12 months will be compared between the intervention and control groups. A linear regression model will be used to compare the groups with weeks of driving as a covariate. Mobility and community participation will also be compared between the two groups using a similar analytic approach. A subgroup analysis will be performed on each primary outcome defined by the cut-off on DriveSafe/DriveAware [1], for needing further assessment (95 and below). As the primary analysis is based on multiple endpoints (3), the results will be interpreted with caution if the statistical significance is borderline (i.e., a *p*-value between 1.66% and 5%) due to multiplicity issues. Continuous secondary outcomes will be analysed using linear regression models with generalized estimating equations for repeated measures (e.g., weekly radius from home) and count data analysed using Poisson or negative binomial regression models as appropriate. Analyses will be conducted using the SAS and STATA software packages.

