**Discussion:**

This randomised trial is powered to provide an objective assessment of the efficacy of an individually tailored education and alternative transportation program to promote safety of older drivers but maintain mobility. Trial registration: Australian New Zealand Clinical Trials Registry ACTRN12612000543886.

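### At the stated rate of 0.73 incidents per person-year, 178 per arm gives about 40% power for IRR 0.80, not 80%, and the planning figures contradict one another

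*Protocol article*

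**What the plan says.** The calculation is in the protocol article under Sample size and statistical analysis. It starts from 12% of older drivers reporting a crash in a year, adds that "near misses are approximately 18 times higher than crash rates", and concludes that the trial should see "approximately 370 incidents (crashes and near misses) during our period of observation (rate 0.73 per person/year". It then sets a "5% level of significance and 80% power" and states: "we require 178 in each arm to detect a 20% reduction in combined crash and near miss rates (i.e., IRR=0.80". After 5% drop-out, 380 drivers are enrolled, 190 per arm. Each is monitored for 12 months.

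The outcome actually analysed is defined under Outcome assessment, Safety: "Rapid deceleration events will be defined as 500 m-G or higher deceleration". The Discussion part of the abstract says: "This randomised trial is powered to provide an objective assessment of the efficacy".

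**The concern.** A rate of 0.73 per person-year over one year gives few events per driver, and a 20% reduction is a modest effect. Together they call for far more than 178 per arm. The figures leading to 0.73 also do not follow from one another, although the text presents them as a chain of reasoning. Finally, the calculation concerns crashes plus near misses, while the trial counts rapid deceleration events (RDE).

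This is the only power calculation given for a safety outcome, and it leads directly to the enrolment of 380. If the 80% claim is accepted, a null RDE result risks being read as evidence against a 20% reduction that the trial was unlikely to detect.

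**Working it through.** **Inputs** (Sample size and statistical analysis): significance level 5%; power 80%; rate 0.73 per person-year, taken as the control rate; IRR 0.80, so the intervention rate is 0.73 × 0.80 = 0.584; 178 per arm. Follow-up is one person-year each. Sidedness is not stated; two-sided is assumed and one-sided is shown as well.

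**Reproducing 178.** No rate formula tried gives 178 at 0.73. Two other routes come close:
- Treating 0.73 and 0.584 as proportions (difference 0.146, mean 0.657): n = [1.96√(2 × 0.657 × 0.343) + 0.8416√(0.73 × 0.27 + 0.584 × 0.416)]² / 0.146² = 164.8. With continuity correction, (164.8/4) × [1 + √(1 + 4/(164.8 × 0.146))]² = 178.2.
- A Poisson comparison with a control rate of 2.0 per person-year: 177.3.

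The first is not valid for a rate of recurrent events, and the second is not the stated rate. Either may be the origin; the document does not say.

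**Sample size at the stated rate.** Poisson comparison on the log scale:

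n per arm = (1.96 + 0.8416)² × (1/0.73 + 1/0.584) / (ln 0.8)² = 7.849 × 3.082 / 0.0498 ≈ 486.

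Other versions: rate difference 484; square-root transform 483; 0.73 read as the average over both arms 438; one-sided test 383.

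**Power at 178 per arm.** SE of the log rate ratio = √(3.082/178) = 0.1316. Then 0.2231/0.1316 − 1.96 = −0.264, a power of 39.6%; a simulation gave 39.7%. With 190 per arm it is 41.8%, and one-sided at 178 it is 52%. Solving the formula for the ratio at n = 178 gives a detectable IRR of about 0.68.

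**Consistency of the inputs.**
- 0.12 × 18 = 2.16 near misses per person-year; adding the crashes, 0.12 × 19 = 2.28. The text has 0.73.
- 0.73 × 380 = 277 incidents. The text has about 370.
- 370/380 = 0.97 per person-year.
- 370/0.73 = 507 person-years, but 380 drivers over 12 months supply at most 380.
- The drop-out step is sound: 178/0.95 = 187.4, so 190 per arm is enough.

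**Power at 178 per arm under each printed figure** (Poisson, two-sided, IRR 0.80):

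| Figure taken as true | Power |
|---|---|
| 0.73 per person-year | 40% |
| about 370 incidents | 50% (control rate 0.97) to 57% (370 events in all) |
| 2.16 to 2.28 per person-year | 83% to 85% |

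In total, 80% power needs about 631 events.

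**Overdispersion** (the dispersion k is an assumption; the documents give none). A negative binomial model adds 2k to the bracket:
- At 0.73, k = 0.5 to 1 gives 644 to 802 per arm, and power at 178 of 31% to 26%. The detectable IRR at k = 1 is about 0.61.
- At 2.28, k = 0.5 gives SE = √((0.4386 + 0.5482 + 1)/178) = 0.1057 and 0.2231/0.1057 − 1.96 = 0.15, a power of 56%. With k = 1, power is 41%.

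**The case against.** The strongest reply is that 40% is conditional. If the inputs conflict, no single power figure can be called the trial's own, and at 2.16 to 2.28 per person-year the 80% claim stands under a Poisson model. That is correct, and the 40% must always be tied to 0.73. It does not rescue the text, because it requires giving up both the printed rate and the printed incident count, and the printed count alone reaches only 50% to 57%.

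Second, the article presents deceleration as a possible indicator of near-crashes, so RDE is a declared proxy and not an unrelated outcome. This narrows the criticism. Crashes plus near misses are still not a listed outcome, and nothing shows that events at the chosen threshold occur at the planning rate.

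Third, the dispersion values are not in the documents, and the origin of 178 is conjecture. Both points stand, but the main result needs neither. It is also true that the plan assigns linear regression to RDE and mentions negative binomial models only for secondary counts. Extra variation between drivers reduces power under either model, so the calculation should allow for it.

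Fourth, the article describes the 30-vehicle field test only in terms of data quality and trip capture, so it may hold no RDE rates. The abstract sentence gives no power figure, and the sample size section also cites distance and participation. These points affect how the remedy is worded, not the error.

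**Conclusion.** The point holds. On the stated rate, ratio, significance level and follow-up, 178 per arm gives about 40% power instead of 80%, and about 486 per arm would be needed. This rests on a two-sided test, one person-year per driver, 0.73 as the control rate and no overdispersion. One-sided testing (383 per arm) or reading 0.73 as the overall rate (438) does not close the gap, and overdispersion widens it. Separately, 12% with a factor of 18, the rate of 0.73 and the count of 370 cannot all be right. Power cannot be settled until they are reconciled: the printed figures allow anything from 40% to 85% under Poisson. The power claim is also not tied to RDE, the outcome that will be analysed. The statement is wrong as written and must be corrected.

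**What to change.** Keep 380 participants and rewrite the sample size paragraph:

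- State one baseline rate, its source and whether it is the control or the overall rate, and give the expected number of events that follows from it.
- Replace the 80% claim at IRR 0.80 with the power that rate gives, or with the ratio detectable at 80% power. If 0.73 stands, these are about 40% and about 0.68 before overdispersion.
- Do the calculation for RDE under a negative binomial model. Take rate and dispersion from the 30-vehicle field test if it recorded such events; otherwise show a stated range and label it as assumed. State the sidedness of the test.
- Bring the abstract's sentence about power into line.

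The cost is one reworded paragraph, one abstract sentence and a less favourable stated power. No participants are added and the design is unchanged.

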We know that lack of alternative transportation keeps older drivers on the road, independent of deficits in vision or cognition [16] and the need for alternate transport was reinforced in our community consultation. In the Hills district, in addition to limited bus routes, two types of community transportation services are available for seniors, firstly social outings in community buses and secondly door-to-door services. The latter run at subsidised cost (i.e., a volunteer gets paid per km to transport the user). The Australian Bureau of Statistics estimates that during a fortnight, those aged 75 and over primarily take trips for shopping (>80%), visiting relatives and friends (58%) but also medical appointments, church or other outings [30]. As part of the intervention delivered in this study, using an occupational therapy problem solving process [59], participants are encouraged to consider life without a licence and devise a plan for staying active, connected and independent within their community when they retire from driving. To formulate this plan, an inventory of desired trips will be taken and the participant counselled about alternatives to driving, utilising public transport, door to door community transport, and council community buses.

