### Process evaluation

Measuring intervention implementation in trials has gained momentum in recent decades [69-71] to safeguard against discarding ineffective interventions that were poorly executed or adopting effective interventions that are impractical to implement in the real world [72]. Our intervention, like many complex health interventions, may have several potential ‘active ingredients’ for intervention success or failure [70,73]. By exploring the relationship between intervention outcomes and the quality of intervention implementation, we propose to pinpoint the ‘active ingredients’ responsible for intervention outcomes [70,71,73]. Our process evaluation has three main aims: to measure what is taught (treatment fidelity and dose delivered), what is learnt (dose received), and what is actually used (treatment enactment) [69].

When measuring program fidelity, caution needs to be exercised to avoid overly standardising complex interventions [73,74]. In our intervention, two individualised, one-to-one sessions will address driving self-regulation and planning for retirement from driving. The underlying behavourial theory is standardised, allowing the form of the intervention to be tailored to meet the specific behaviour change needs of participants. There is growing consensus that complex interventions have greater potential for success if they are tailored to the local context [70,73,74].

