## Discussion

Older drivers have high crash involvement and increased vulnerability to injury on the road, however driving is vital to independence for many older Australians. While programs to promote safe mobility are in place, there are few that have been evaluated for their effectiveness. Results from the small number of randomised trials evaluating interventions to promote safety but maintain mobility are mixed [76] and there are no proven strategies to protect older drivers but maintain their mobility [6]. Here we evaluate a safe mobility program which was developed in the United States but adapted for the Australian setting. The program has been adapted in consultation with the community, draws on existing seniors’ mobility services in the local area and employs a validated educational programs for older, at-risk drivers. Therefore the program has the potential to be sustainable. Furthermore the program is based on robust behaviour change theory and delivery of the program will be individualised according to the stages of the precaution adoption model. While there are a number of initiatives from bodies such as motoring associations, local councils and seniors groups, many are not sustained, in part due to the lack of proof of their effectiveness. This randomised trial will provide credible evidence about the efficacy of a safe transport program, using objective measures of driving ability.

The results will have relevance to policy makers and advocates for older members of the community in high income countries internationally, where there is high reliance on private motor vehicles and an ageing population. If proven to be effective, this program could be made available to older members of the community to assist in the timely retirement from driving and continued independent mobility and community engagement. Findings from this research will provide high quality, policy relevant evidence regarding the potential to prevent crash injuries and maintain mobility during the transition to not driving. If proven, this integrated program will help older Australian live productively, independently and safely in the community.

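### The primary model for 12-month kilometres and rapid deceleration events adjusts for weeks of driving, which accrue after randomisation and which the programme can change, so its coefficient is not the intention-to-treat effect

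*Protocol article*

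**What the plan says.** All references are to the protocol article. Under *Sample size and statistical analysis* it names the comparison, "Driving exposure (kilometres travelled) and the number of rapid deceleration events (RDE) during 12 months will be compared between the intervention and control groups", and then the model, "A linear regression model will be used to compare the groups with weeks of driving as a covariate". The same paragraph opens with "An intention-to-treat approach will be used for all analyses". For the third primary outcome, the Keele Assessment of Participation (KAP), it says only "Mobility and community participation will also be compared between the two groups using a similar analytic approach".

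Elsewhere the article makes driving itself the target of the programme:

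- *Safety*: "A primary aim of this research will be to determine if driving safety is promoted through reduced driving exposure and fewer rapid deceleration events".
- *Intervention*: participants are to "devise a plan for staying active, connected and independent within their community when they retire from driving".
- *Process evaluation*: "two individualised, one-to-one sessions will address driving self-regulation and planning for retirement from driving". This section also uses change in driving exposure as its measure of whether treatment was enacted.
- *Discussion*: the programme, if effective, could "assist in the timely retirement from driving and continued independent mobility".

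*Randomisation* places allocation after the baseline assessment. Weeks of driving is nowhere defined as a baseline value, as weeks of device monitoring or as an offset.

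**The concern.** Twelve-month kilometres are the number of weeks driven multiplied by the kilometres per driven week. A programme that leads someone to stop at week 20 has reduced that person's exposure, which is what the trial sets out to measure. A model that holds weeks of driving fixed compares this person with controls who drove equally few weeks. What remains is closer to an effect on driving intensity than to the effect of being allocated to the programme.

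The same reasoning applies to RDE counts, since events can occur only while driving. At stake are the meaning and size of two of the three primary estimates, some power, and the consistency of the model with the intention-to-treat promise. The attenuation appears only if the programme succeeds in one of the ways the article describes, by bringing forward retirement from driving.

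**Working it through.** **1. What the article supplies.** It gives no expected effect on weeks driven, so there is no figure of its own to reproduce for this point. Two inputs are usable. *Background* gives retirement from driving as 3-5% a year; 4% is used for controls. The sample-size section calls 6 km/day about a 30% reduction, so the control mean is 6/0.30 = 20 km/day, or 140 km/week. Assumptions: CV 0.9, lognormal weekly kilometres, uniform stopping times over 52 weeks, 180 per arm, and intervention-arm retirement of 12% or 20%.

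**2. Direction.** For least squares with arm and weeks W in the model,

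unadjusted difference = adjusted difference + c × (mean W, intervention − mean W, control),

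where c is the slope on weeks. Since c is positive for kilometres, fewer driven weeks in the intervention arm always shrink the estimated reduction.

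**3. Size by hand.** With retirement share r and uniform stopping, the mean share of the year driven is 1 − r/2: 0.98 at 4%, 0.94 at 12% and 0.90 at 20%. Control kilometres are 140 × 52 × 0.98 = 7,134.

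- *4% versus 12%, total reduction 27%.* Weekly kilometres in the intervention arm are multiplied by 0.73 × 0.98/0.94 = 0.761, giving 106.5 km/week. The weeks differ by 52 × 0.04 = 2.08. Most stopping is in the intervention arm, so c is near 106.5. The amount removed is 2.08 × 106.5 = 222 km, or 3.1 points, leaving 23.9%. Taking c as high as 140 would leave 22.9%.
- *4% versus 20%, total reduction 28%.* The multiplier is 0.72 × 0.98/0.90 = 0.784, giving 109.8 km/week. The weeks differ by 4.16. The amount removed is 457 km, or 6.4 points, leaving 21.6% (19.8% with c = 140).

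**4. Size by simulation** (least squares with and without weeks):

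| Retirement, control vs intervention | Total reduction in km | Weeks-adjusted estimate | Power, unadjusted to adjusted |
|---|---|---|---|
| equal | 28% | 28% | 93% to 93% |
| 4% vs 12% | 27% | about 24% | 92% to 85% |
| 4% vs 20% | 28% | about 22% | 93% to 74% |

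A repeat of 4,000 trials per scenario gave 26.9% to 23.5% (power 90% to 80%) for the second row, and 28.0% to 24.7% (92% to 85%) when the total reduction was set at 28%. The third row gave 28.1% to 21.4% (91% to 72%). The effects are therefore good to about one point and the powers to about five.

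**5. Same check on the article's own distance figures.** The SD implied by 6 km, 178 per arm and 80% power is 6/((1.960 + 0.842) × √(2/178)) = 20.2 km/day. For a true 30% reduction and 4% of controls stopping, the share of the effect removed is 0% if 4% of the intervention arm stop, 8% if 10% stop (power 0.91 to 0.86), 22% if 20% stop (0.89 to 0.70) and 37% if 30% stop (0.89 to 0.51). Unadjusted power exceeds 0.80 because a proportional reduction also narrows the spread in the intervention arm.

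**6. What a much larger loss would need.** Suppose active weeks fall from 93% to 81% and weekly kilometres fall by 15%. A 28% reduction is then estimated as 14%, and power falls from 93% to 30%. Retirement cannot produce this alone: with 5% of weeks skipped in both arms, 4% versus 12% retirement gives 0.95 × 0.98 = 93% and 0.95 × 0.94 = 89%. Reaching 81% requires continuing drivers to be active in only 0.81/0.94 = 86% of weeks, so skipping about 14% of weeks against 5% in controls. No section supports that.

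**The case against.** The strongest reply is that weeks of driving is undefined and may mean weeks with driving data recorded. Recording time will vary, since 5% drop-out is expected, and a 12-month total needs some allowance for it. On that reading the covariate is observation time and the harm is smaller. This stands as a reason to define the term. It does not rescue the sentence, because the article never gives that meaning, and observation time would normally enter as a denominator or offset, with monitored weeks without driving counted as zero.

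Three stronger readings are tempting and should not be made.

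- *KAP is adjusted for weeks of driving too.* A reader might infer this from the similar approach promised for participation. The words do not settle it: they may mean only linear regression between groups. KAP is collected at baseline, and *Safety* adjusts 12-month survey responses for baseline. The point for KAP is to exclude the covariate explicitly, because it has no role there as exposure time.
- *Power collapses.* This needs the widespread skipping of whole weeks in step 6, or an effect that runs entirely through weeks driven, in which case a near-zero adjusted estimate is built in.
- *The repair is wording only, because the uploads show device status.* The article describes transmission while the vehicle is operating and weekly transfer to a server. It does not show that a silent week can be identified automatically as no driving or as a fault.

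**Conclusion.** The concern holds. As written, the primary model for kilometres and RDE conditions on a post-randomisation component of driving exposure that the programme is meant to be able to change, and this conflicts with the intention-to-treat statement in the same paragraph.

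The direction for kilometres follows from algebra; the size does not follow from the documents. Under the stated assumptions it runs from no loss when weeks driven are equal, through about 3 points of a 27% reduction at 12% retirement, to about 6 points of a 28% reduction at 20% retirement. The 12% and 20% are assumptions, set against the article's background rate of 3-5%. If the programme only shortens or thins trips within weeks, little is lost. The loss for RDE was not quantified, and an effect on KAP is not established.

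**What to change.** - Remove weeks of driving from the primary kilometre and RDE models.
- If observation time must be accounted for, use the time from randomisation that the device was installed, up to removal or withdrawal, as a rate denominator or offset.
- Count installed time after a participant stops driving as zero kilometres and zero RDE. Treat known device failures as missing.
- State that the KAP model does not include weeks of driving and adjusts for the baseline KAP score already collected.
- Keep any analysis by weeks driven as a labelled supplement.

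The change is to the analysis only; it needs no extra participants or outcome assessments. It is not free: installation, removal and withdrawal dates must be recorded, and silent weeks must be classified as no driving or device fault, which the article does not show the uploads can do automatically. The rule for that classification should be fixed without knowledge of allocation, since coding faults as zero would introduce an error of its own.
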